#### 4.7 Statistical Analysis:

The primary research outcomes for this study are rectal temperature (Tre), rate pressure product (RPP), heart rate (HR), blood pressure (BP), thermal sensation (TS), thermal comfort (TC) and pre to post trial whole-body sweat losses (WBSL). Secondary outcomes to be compared are skin temperature (TSk), limb blood flow (LBF), skin blood flow (SkBF), local sweat rate (LSR), cognitive performance, rating of nausea and light headedness (NL), and evidence of orthostatic hypotension (OH). All data will be compared between all four interventions and both conditions (very hot and dry, and hot and humid). To assess the primary and secondary outcome variables, pre to post trial changes as well as the means of the dependent variables will be analyzed using one-way repeated measures ANOVAs with the repeated factor of cooling intervention (four levels: no fan (NF), fan (F), fan and skin-wetting (FSW), and no fan and skin-wetting (NFSW)) will be employed. If significant main effects or interactions are found, independent differences will be assessed using a two-tailed paired Student's t-tests while maintaining a fixed probability (5%) of making a type I error using a Holm-Bonferroni correction. All statistical analyses will be performed with GraphPad Prism (version 6.0, GraphPad Software, La Jolla, CA).

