## 6- Statistics

### 6.1 Sample size

The sample size computation is based on comparison of the primary endpoint (change in rate pressure product from baseline to the end of a 3 hour simulated heatwave exposure to 38°C and

60% RH) between the 4 conditions of control, fan use alone, skin wetting alone, fan use + skin wetting.

The mean and standard deviation of the change in rate pressure product were taken from the preliminary data presented in Figure 3 and are expected to range between 1000 bpm x mmHg and 1700 bpm x mmHg for the mean and between 1700 bpm x mmHg and 2000 bpm x mmHg for the standard deviation. The standard deviation of the difference between conditions is expected to be similar.

The main interest is to compare the control condition with the 3 other conditions taken individually, which implies a significance level of 0.0167 ( $0.05 / 3$ ). A difference of 1250 bpm x mmHg in change in rate pressure product between the control condition and any other condition is judged to be clinically relevant.

In this context a sample size of 30 participants will give 80% power to detect a difference of 1250 bpm x mmHg in change between the control condition and any other condition, assuming that the standard deviation of the difference between conditions is 2000 bpm x mmHg and using a paired t-test with a 0.0167 two-sided significant level. To account for an approximately 10% loss to follow-up rate, 34 participants will be included in the study. Of the 34 participants, 17 will be taking beta-blockers whereas the other 17 will not be taking beta-blockers.

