## 5 STATISTICAL METHODOLOGY

### 5.1 Statistical Considerations

Statistical analyses will be performed using SAS Version 9.4 or higher. Unless otherwise specified, all statistical tests will be two-sided and performed at a significance level of 0.05.

Prior to all parametric analyses, basic assumptions will be checked and if they are violated, non parametric analyses will be performed to confirm results from the parametric analyses. If outliers are identified, analysis with and without the outliers may be presented.

In the event that a participant did not complete the 180 minutes heatwave exposure, the change from baseline will be calculated using the last measure available.

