#### 5.2.1 Primary Analysis

The following descriptive statistics will be presented for the primary endpoint (change from baseline in rate pressure product) under the 38°C and 60% RH heatwave exposure: mean, standard deviation, median, Q1, Q3, minimum and maximum.

A restricted maximum likelihood (REML)-based linear mixed model including a term for condition and accounting for repeated measures, will be used to compare the change from baseline in rate pressure product under the 38°C and 60% RH heatwave exposure under the following conditions: control, fan alone, skin wetting alone and fan + skin wetting. Contrasts under this model will allow for the three main comparisons:

- Control vs. fan alone
- Control vs. skin wetting alone
- Control vs. fan + skin wetting

Differences between the control condition and each of the 3 other conditions will be tested and presented with point estimate along with 98.33% confidence intervals. These three comparisons will be tested at the 0.0167 significance level to control for the multiplicity of tests.

The assumption of normality underlying this model will be checked.

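### SAP 5.2.1 tests the three control contrasts at a fixed 0.0167. This is valid, but Holm on the same contrasts would keep 5% family-wise error and never reject fewer.

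*Supplement*

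**What the plan says.** The SAP covers the combined data of the Sydney and Montreal studies. Section 5.2.1 names three contrasts (control against fan, against skin wetting, and against fan plus skin wetting). Each is to be "tested and presented with point estimate along with 98.33% confidence intervals". On the error rate, the section adds this rule: "These three comparisons will be tested at the 0.0167 significance level to control for the multiplicity of tests". Section 5.1 sets the default: "all statistical tests will be two-sided and performed at a significance level of 0.05".

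The latest Montreal protocol has the same rule in its section 6.2. Its section 6.1 derives the level from 0.05 / 3 ("which implies a significance level of 0.0167") and sizes the study on it.

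The latest Sydney protocol, section 4.7, names a different correction. Its pairwise tests are to be run "while maintaining a fixed probability (5%) of making a type I error using a Holm-Bonferroni correction". They open only on a condition: "If significant main effects or interactions are found, independent differences will be assessed using a two-tailed paired Student's t-tests". The section does not list which pairs are to be tested. The SAP does not mention this rule.

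**The concern.** Two points raise the question. First, the pooled data come partly from a study whose protocol names Holm-Bonferroni, while the SAP uses a fixed threshold and does not say that it replaces the other rule. Second, on a given set of three contrasts, fixed Bonferroni is never more powerful than Holm at the same family-wise error.

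The SAP's primary hypothesis is that control is worse than each of the three strategies, so each contrast is a conclusion in its own right. The choice of rule can change which strategies are declared better than control. The difference is largest when several strategies work, which is what the hypothesis expects.

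**Working it through.** **Inputs.** From Montreal 6.1: "A difference of 1250 bpm x mmHg in change in rate pressure product between the control condition and any other condition" is taken as clinically relevant; "assuming that the standard deviation of the difference between conditions is 2000 bpm x mmHg"; n = 30; paired t-test, two-sided 0.0167; stated power 80%. Three assumptions are not in the documents: equal variances and correlations across conditions (so two contrasts sharing the control correlate 0.5), paired t-tests in place of the SAP's mixed model, and a pooled n of 75 (30 Montreal + 45 Sydney, the two planned numbers before dropout inflation).

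**1. The plan's own figure.** Level: 0.05 / 3 = 0.0167, and 1 − 0.05/3 = 98.33%, so test level and interval level agree. Noncentrality = 1250 / (2000/√30) = 3.42. The critical t with 29 df at two-sided 0.0167 is 2.54. Exact power is 80.5%, and 30 is the smallest n that reaches 80%. The stated figure is reproduced.

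**2. Why Holm dominates on the same contrasts.** Holm orders the p-values and compares them with 0.05/3 = 0.0167, 0.05/2 = 0.025 and 0.05/1 = 0.05, stopping at the first failure. Any p-value at or below 0.0167 passes every step it can meet, so nothing the fixed rule rejects is lost. If m of the three nulls are true, the first true null to be rejected must pass a threshold no larger than 0.05/m. By the Bonferroni inequality the family-wise error is then at most 5%, whatever the correlation.

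Illustration with p = 0.010, 0.020, 0.040:
- The fixed rule rejects one.
- Holm on these three contrasts rejects all three (0.010 ≤ 0.0167, 0.020 ≤ 0.025, 0.040 ≤ 0.05). The adjusted p-values are 3 × 0.010 = 0.030, 2 × 0.020 = 0.040 and 0.040.

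**3. Size of the gain at n = 30** (100,000 simulated trials, SD of every difference 2000):

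| True differences | Power per effective contrast, fixed | Holm | At least one rejection (both rules) |
|---|---|---|---|
| 1250, 1250, 1250 | 80.4% | 87.5% | 95.5% |
| 0, 1250, 1250 | 80.3% | 83.5% | 92.2% |
| 0, 0, 1250 | 80.4% | 80.5% | 81.4% |
| 0, 0, 0 | – | – | 4.5% |

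With all three effective, the chance of showing all three rises from 61.2% to 78.5%.

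**4. Size at the assumed pooled n = 75.**
- All three 1250: 99.8% per contrast under the fixed rule and at least 99.9% under Holm.
- All three 700: noncentrality = 700 / (2000/√75) = 3.03. Power per contrast is about 72% fixed and 80% Holm; for all three, about 49% and 68%.
- Differences 400, 800, 1250: the 400 contrast has 24.3% against 39.6%, the 800 contrast 84.2% against 88.2%, and the 1250 contrast 99.8% under both.

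**5. Sydney 4.7 is a different procedure.** It opens only after a significant ANOVA, and four conditions give six possible pairs. If all six are tested, the first Holm threshold is 0.05/6 = 0.0083. On that reading, simulated power at n = 30 with all three effective is 75.0% per contrast, about 5 points below the SAP's fixed rule.

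**The case against.** The strongest reply is that the SAP contains no fault here. A pooled analysis of two studies with different rules has to choose one. The SAP chose the Montreal rule, on which that study was sized, and stated it without ambiguity. Family-wise error is controlled and the planned power is met. This stands.

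The fixed rule also buys something: each 98.33% interval excludes zero exactly when its test is significant. Holm gives that up, because a contrast rejected at step 2 or 3 may have a 98.33% interval that includes zero. A reader might infer that the SAP gives up power with nothing in return, and the documents do not support that.

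A reader might also infer that adopting Holm would simply restore the Sydney rule. It would not. Sydney's step is gated by an ANOVA over an unlisted set of pairs, and read as six pairs it has less power than the SAP rule. The p-value illustration above applies to Holm on the SAP's three contrasts, not to Sydney 4.7. If 0.010 were the smallest of six p-values, Sydney's rule would reject none, because 0.010 > 0.0083.

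Finally, the larger gains at n = 75 need effects below 1250. The 700 is only the spread of the preliminary means (1700 − 1000). Those means come from young adults at 46°C and 10% RH for 2 hours, and fan use there gave a higher rate pressure product than control. The 700 scenario is therefore illustrative and not a forecast for the primary condition.

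What survives is narrower: on the SAP's own three contrasts, Holm rejects at least as much at the same error rate, and the cost in interval agreement can be handled with a note.

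**Conclusion.** This is an optional, low-cost improvement and not an error. The fixed 0.0167 rule is valid and is the one rule for the pooled analysis. Holm on the same contrasts keeps the plan's 80% power as a floor. At n = 30 with differences of 1250, it adds about 7 points per effective contrast if all three strategies work, 3 if two work and 0 if one works. It adds nothing to the chance of finding at least one effect. At an assumed n = 75 the gain is negligible for differences of 1250, about 8 points per contrast for three differences of 700, and about 15 points for the weakest of 400, 800 and 1250.

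The dominance and the 5% error bound are general. The sizes rest on the SD of 2000, equal correlations between conditions, paired t-tests in place of the REML model, and a pooled n that the SAP does not state.

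**What to change.** In SAP 5.2.1:
- Replace the fixed threshold by Holm on the three named contrasts: order the p-values, compare them with 0.0167, 0.025 and 0.05, and stop at the first non-significant result. Apply no ANOVA gate.
- Report Holm-adjusted p-values and keep the 98.33% intervals.
- State that decisions follow the adjusted p-values, because the interval may include zero for a contrast rejected at step 2 or 3.
- State that this rule supersedes section 4.7 of the Sydney protocol for the pooled analysis.

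The cost is a few sentences and the loss of exact agreement between test and interval at steps 2 and 3. No data collection, model or sample size changes. If the sponsor prefers to keep the fixed rule for its matching intervals, the last statement alone is still worth adding.

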### 5.2.2 Secondary Analysis

Descriptive statistics (mean, standard deviation, median, Q1, Q3, minimum and maximum) will be presented for the change in rate pressure product from baseline to end of a 3-hour simulated heatwave exposure at 45°C and 15% RH. The change in rate pressure product will be analyzed using a REML-based linear mixed model including a term for condition and accounting for repeated measures. Contrasts under this model will allow for the three following comparisons:

- Control vs. fan alone
- Control vs. skin wetting alone
- Control vs. fan + skin wetting

The difference between the control condition and each of the 3 other conditions will be presented with point estimate along with 95% confidence intervals.

### 5.2.3 Tertiary Analysis

To study the impact of beta-blockers on the effect of the cooling interventions, change in rate pressure product will be analyzed using a REML-based linear mixed model, accounting for repeated measures, including a term for condition (control, fan alone, skin wetting alone and fan + skin wetting), a term for beta-blockers (yes/no) and a term for the interaction between condition and beta-blockers. This interaction will be tested at the 0.10 significance level and will determine whether the condition effect is impacted by taking beta-blockers. Condition effects will be estimated and presented with 95% confidence interval within subgroup of beta-blockers (yes/no). This analysis will be conducted on the subset of subjects with coronary artery disease (CAD) under the 38°C and 60% RH heatwave exposure. The same analysis will also be conducted in the subset of subjects with CAD under the 45°C and 15% RH heatwave exposure, with condition being restricted to control and skin wetting.

Under each of the heatwave exposures separately, change from baseline in core temperature, whole-body sweat rate, thermal comfort and thermal sensation will be presented and analyzed as the primary endpoint using a REML-based linear mixed model, but 95% confidence intervals will be presented with the point estimates and comparisons will be tested at the 0.05 significance level.

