### 5.2.4 Other Subgroup Analysis

Subgroup analyses will be performed for the change in rate pressure product, looking at the homogeneity of the condition effect across the following factors: Sex (Female/ Male) and Site (Montreal/ Sydney).

The subgroup analyses will be conducted using a REML-based linear mixed model, accounting for repeated measures, including a term for condition, a term for the subgroup factor and the condition x subgroup factor interaction. This interaction will be tested at the 0.10 significance level and will determine whether the condition effect is impacted by the presence of the factor. Condition effects will be estimated and presented with 95% confidence interval within subgroups.

The subgroup analysis will be conducted separately under each of the heatwave exposures and will be considered exploratory.

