### 5.2.5 Other exploratory Analysis

To take into account a potential acclimation effect that could occur during the summer, the change in rate pressure product will be analyzed using a REML-based linear mixed model, accounting for repeated measures, including a term for condition, a term for the season (Summer/Not Summer) and the condition x season interaction. This interaction will be tested at the 0.10 significance level and will determine whether the condition effect is impacted by the season. Condition effects will also be estimated and presented with 95% confidence interval within the season category.

The category “Summer” will be assigned to visits that occurred in June, July, August or September at the Montreal site and to visits that occurred in November, December, January, February, March or April at the Sydney site. Otherwise, the “Not Summer” category will be assigned. As season may vary across study visits of a same subject, it will be considered a within-subject factor in the analysis model.

This analysis will be conducted separately under each of the heatwave exposures and will be considered exploratory.

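### The SAP lets a 0.10 interaction test settle whether beta-blockers change the cooling effect, but plans no estimate of the between-group difference and cannot support a conclusion of no impact

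*Supplement*

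**What the plan says.** SAP 5.2.3 fits a mixed model with condition, beta-blocker use and their interaction, and states: "This interaction will be tested at the 0.10 significance level and will determine whether the condition effect is impacted by taking beta-blockers". The population is restricted: "This analysis will be conducted on the subset of subjects with coronary artery disease (CAD"). Under the hot-dry exposure only control and skin wetting are compared.

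SAP 5.2.4 applies the same rule to sex and site; the test "will determine whether the condition effect is impacted by the presence of the factor". SAP 5.2.5 does so for season; the test "will determine whether the condition effect is impacted by the season". Each section presents condition effects with 95% intervals within subgroups. None plans an estimate or interval for the interaction contrast. Tests are two-sided under SAP 5.1.

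The beta-blocker question is a tertiary (exploratory) objective in SAP 2.2. Section 6.1 of the latest Montreal protocol divides the sample for it: "17 will be taking beta-blockers whereas the other 17 will not be taking beta-blockers". No power is given for any interaction.

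**The concern.** The wording turns an interaction p-value into a yes/no finding. Below 0.10 the effect counts as impacted; at or above 0.10 the natural reading is that it does not. The second half is unsafe when the test is weak, and the number of CAD patients was set by a within-person comparison, not by a comparison between two groups of about half that size.

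The quantity of interest is how far the control-versus-strategy effect differs between patients with and without beta-blockers. Two separate within-group intervals do not state that difference or its uncertainty. They also invite the mistake of reading an effect that is significant in one group only as evidence of modification.

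At stake is the answer to a named objective. The Montreal protocol's literature review suggests that patients on beta-blockers may gain most from fan use with skin wetting, so an unsupported statement of no impact would bear directly on that idea.

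**Working it through.** **Inputs (Montreal protocol 6.1 unless noted).** 34 enrolled, 17 per beta-blocker group; about 10% loss, hence 30 evaluable, or 15 per group if loss is equal. The SD is taken as "assuming that the standard deviation of the difference between conditions is 2000 bpm x mmHg", with 1700 as the lower end of the protocol's range. Interaction alpha is 0.10 (SAP 5.2.3), two-sided. Size of interaction: 1250, by assumption. The protocol's statement is "A difference of 1250 bpm x mmHg in change in rate pressure product between the control condition and any other condition is judged" clinically relevant, which concerns a condition effect and not a difference in effects between groups.

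**The plan's own figure.** Paired t-test, n = 30, two-sided 0.0167: noncentrality = (1250/2000) × √30 = 3.42, df 29, power 80.5%. The protocol states 80%. 30/0.9 = 33.3, rounded up to 34. Both reproduce.

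**Beta-blocker interaction, one contrast.** This is a two-sample comparison of the within-person difference (control minus strategy). SE = SD × √(1/n + 1/n), noncentrality = 1250/SE, df = 2n − 2. Power is from the noncentral t at two-sided 0.10. The 95% half-width is t(0.975, df) × SE.

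| SD | Per group | SE | 1250/SE | Power at 0.10 | 95% half-width |
|---|---|---|---|---|---|
| 2000 | 15 | 730 | 1.71 | 51% | 2.048 × 730 = 1496 |
| 2000 | 17 | 686 | 1.82 | 56% | 2.037 × 686 = 1397 |
| 1700 | 15 | 621 | 2.01 | 63% | 2.048 × 621 = 1272 |
| 1700 | 17 | 583 | 2.14 | 67% | 2.037 × 583 = 1188 |

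At SD 2000, 80% power would need about 33 per group.

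**Overall three-df test, humid exposure.** Under compound symmetry (residual variance SD²/2) and SD 2000, power is 50.5–55% if one strategy, or all three equally, differs by 1250. It is 62–67% if two strategies differ and 38–45% for graded differences. Under the hot-dry exposure there is only one contrast, so the table applies at best.

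**Sex and site.** In the combined sample, for the same difference and SD 2000, the one-contrast power is 84% with 30 v 45 and 90% with 45 v 45. This assumes the Montreal SD holds in Sydney and is less favourable under the hot-dry exposure, where Sydney visits are optional. Season cannot be computed because the split of visits is not given.

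**Number of tests.** Beta-blockers, sex, site and season under two exposures make 4 × 2 = 8 tests at 0.10. If no factor modifies the effect, the expected number of false positives is 8 × 0.10 = 0.8, whether or not the tests are independent.

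**The case against.** Much is already tempered. The beta-blocker objective is labelled tertiary (exploratory), and 5.2.4 and 5.2.5 call their analyses exploratory. Using 0.10 in place of the general rule ("all statistical tests will be two-sided and performed at a significance level of 0.05") is itself a concession to low interaction power. Within-subgroup estimates are presented whatever the p-value, so nothing is gated on the test. As the beta-blocker groups contain different people, a reader could roughly rebuild the difference from the two intervals. All of this stands and lowers the stakes. It does not alter what the sentence tells the analyst to conclude, nor supply the missing estimate.

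Four stronger readings are tempting and not supported:

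- That the beta-blocker test misses a clinically relevant difference about half the time. This needs 1250 as the relevant interaction, which the documents do not say, and the top of the SD range. At SD 1700 the miss rate is roughly a third.
- That all the subgroup tests are underpowered. Sex and site draw on both studies and are much better placed.
- That there is a 57% chance of at least one false finding (1 − 0.9^8). This requires eight independent tests. The same participants contribute to both exposures, and site largely coincides with CAD status.
- That the SAP will report equal effectiveness whenever p is at least 0.10. It nowhere says so; it simply leaves the reading of such a result open.

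**Conclusion.** The point holds as a matter of interpretation and reporting. For beta-blockers, power is about 51–56% (SD 2000) or 63–67% (SD 1700) for an interaction of 1250. The 95% interval for the between-group difference would extend about 1190 to 1500 either side of the estimate. In three of the four scenarios even an estimate of zero would leave 1250 inside the interval; in the fourth (17 per group, SD 1700) only an estimate very near zero would exclude it. A p-value of 0.10 or more therefore cannot establish that beta-blockers have no impact.

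This rests on planned and roughly equal group sizes, since the SAP gives no achieved numbers; on an SD between 1700 and 2000 in both groups; and on borrowing 1250 as the size of interaction. For sex, site and season the point is narrower: no interaction estimate is planned, and several tests at 0.10 are unadjusted. No primary or secondary result is affected.

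**What to change.** In SAP 5.2.3, 5.2.4 and 5.2.5:

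- Replace the statement that the test determines whether the effect is impacted with wording that the interaction is assessed.
- Report each interaction contrast, meaning the between-subgroup difference in each control-versus-strategy effect, with a 95% confidence interval beside the p-value.
- State that p of 0.10 or more is not evidence against effect modification and is read through that interval.
- State that p below 0.10 is exploratory, given the number of unadjusted tests.

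An equivalence rule based on ±1250 should not be added. The documents give no support for 1250 as an equivalence margin, and with half-widths of 1188 to 1496 it could almost never be met.

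The cost is a few lines of output from models already planned and less definite subgroup statements. Sample size, visits and models are unchanged.
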